## Abstract

**Background and purpose:**

Current follow-up protocols for adolescent idiopathic scoliosis (AIS) are based on consensus and consist of regular full-spine radiographs to monitor curve progression and surgical complications. Consensus exists to avoid inappropriate use of radiographs in children. It is unknown whether a standard radiologic follow-up (S-FU) approach is necessary or if a patient-empowered follow-up (PE-FU) approach can reduce the number of radiographs without treatment consequences.

**Methods and analyses:**

A nationwide multicenter pragmatic randomized preference trial was designed for 3 follow-up subgroups (pre-treatment, post-brace, post-surgery) to compare PE-FU and S-FU. 812 patients with AIS (age 10–18 years) will be included in the randomized trial or preference cohorts. Primary outcome is the proportion of radiographs with a treatment consequence for each subgroup. Secondary outcomes consist of the proportion of patients with delayed initiation of treatment due to non-routine radiographic follow-up, radiation exposure, societal costs, positive predictive value, and interrelation of clinical assessment, quality of life, and parameters for initiation of treatment during follow-up. Outcomes will be analyzed using linear mixed-effects models, adjusted for relevant baseline covariates, and are based on intention-to-treat principle. Study summary: (i) a national, multicenter pragmatic randomized trial addressing the optimal frequency of radiographic follow-up in patients with AIS; (ii) first study that includes patient-empowered follow-up; (iii) an inclusive study with 3 follow-up subgroups and few exclusion criteria representative for clinical reality; (iv) preference cohorts alongside to amplify generalizability; (v) first study conducting an economic evaluation comparing both follow-up approaches.

Adolescent idiopathic scoliosis (AIS) is a 3-dimensional deformity of the spine and trunk in adolescents that occurs in 2–3% of healthy children [1]. Because severe curves have a negative impact on quality of life in adulthood, patients with AIS are regularly seen for radiographic follow-up to detect curve progression, so that timely treatment can be initiated [2]. Treatment consists of thoracolumbar orthosis (brace) or surgery. The length and intensity of radiographic follow-up after treatment varies widely among physicians and lack of consensus exists on the need for long-term radiographic follow-up.

The current standard of care is based on regular radiographic follow-up as recommended in national and international consensus papers [3-5]. Regular radiographic follow-up leads to multiple radiographs without consequences for individual patient treatment. The developing tissues of adolescent patients are exposed to ionizing radiation, which previously has been associated with an increase in risk of breast and endometrial cancer [6,7]. Although technological advances have reduced the radiation dose tremendously, lack of evidence to support routine radiographic follow-up still warrants investigation of new protocols [8,9]. Additionally, a reduction of radiographs reduces the financial burden on the healthcare system. To optimize follow-up protocols of patients with AIS, an AIS Consortium including Dutch scoliosis treatment centers was established to evaluate a new patient-empowered follow-up protocol.

The purpose of this nationwide study is to evaluate whether a reduction in the number of radiographs can be achieved without negative consequences for individual treatment of patients with AIS, by combining clinical measurements and empowering patients through education and self-management.

The hypothesis is that the patient-empowered follow-up-protocol results in a (cost-)effective and safe reduction of the number of radiographs.

## Methods and analysis

### Study design and setting

A multicenter pragmatic trial, a partially randomized preference trial (PRPT), will be performed in The Netherlands. Dutch scoliosis treatment centers were asked to participate in this study. The PRPT consists of 3 separate randomized controlled trials (RCTs), including patients with AIS who are followed in the pre-treatment, post-brace, or postoperative phase (i.e., subgroups). Alongside the RCTs, prospective patient preference cohorts are included for each follow-up subgroup. In these cohorts, all patients are monitored who are not willing to be randomized to either follow-up arm, but who are still willing to participate in the study and who prefer either follow-up protocol. The follow-up period is 24 months per patient. A flow of the study progress following the CONSORT statement [10] is provided in Figure 1. The study will be reported according to CONSORT guidelines.

**Figure 1 F0001:**
[figure not shown]
CONSORT flow of patients throughout the CURVE study.

### Surgeon expertise

Orthopedic spine surgeons participating in the PRPT have to be competent in both follow-up-protocols. Before local study initiation, all participating local study personnel are obliged to complete an online training module, including questionnaires, in which the study-specific protocols and related procedures are evaluated. Residents can participate under the attending supervising surgeon.

### Patient selection

#### Eligibility

To be eligible for this study, a patient must meet the selection criteria for one of the follow-up subgroups as listed in Table 1 (subgroups: pre-treatment, post-brace, post-surgery).

**Table 1 T0001:** Inclusion and exclusion criteria

**General inclusion criteria**
Patients with adolescent idiopathic scoliosis (AIS). Patients scheduled for follow-up in 1 of the participating centers. Biplanar (posterior-anterior [PA] and lateral) full-spine radiographs within an acceptable period from inclusion. Understanding of the Dutch language. Signed informed consent.
**General exclusion criteria**
Patients with juvenile or infantile idiopathic scoliosis with the diagnosis of onset under the age of 10. Patients who are undergoing brace treatment. Patients who have undergone previous spinal surgery and are undergoing revision surgery.
**Specific inclusion criteria pre-treatment group**
Girls aged ≤ 14 years (i.e., 10–14 years) and boys ≤ 15 years (i.e., 10–15 years). These patients generally have 2 years of remaining skeletal growth [22]. Girls: pre-menarche up to 6 months post-menarche (to estimate end of growth). A primary coronal curve with a Cobb angle of 10–25°. *Note on growth:* to validate the inclusion, growth velocity will be determined to avoid stability of growth (threshold: < 0.4 cm/year [23]). Stability in growth in this study is defined as < 0.2 cm/6 months. At baseline and at 6 months’ follow-up assessment height (cm) will be determined. Growth velocity, i.e., height difference over 6 months, will be calculated. After 1 year the treatment validity of inclusion will be determined and patients who are stabilized will be replaced.
**Specific exclusion criteria pre-treatment group**
Skeletally mature patients.
**Specific inclusion criteria post-brace group**
Patients aged 12–18 years.
Within 3 months after termination of brace treatment.
Minimum of 6 months of brace treatment.
**Specific inclusion criteria post-surgery group**
Patients aged 12–18 years.

#### Recruitment and informed consent

Eligible patients are informed and invited to participate by their local treating orthopedic surgeon. To obtain informed consent, eligible patients and their parents will be handed an age-specific patient information form (PIF). According to Dutch regulations, for each subgroup different PIFs are developed for each age category (10–11, 12–15, and > 15 years of age). The first patients were included in July 2022.

### Randomization and blinding

After obtaining informed consent, patients will either be randomized or allocated to the protocol of their preference. Randomization is performed according to a minimization algorithm in a 1:1 ratio to either the standard follow-up protocol (S-FU) or the patient-empowered follow-up protocol (PE-FU). Randomization will be performed in CASTOR EDC (www.castoredc.com), an online secured study and data-management system with built-in randomization (random permuted block size 2:4). Considering the nature of this project, blinding to the follow-up allocation for patients and medical staff is not possible. The trial statistician will be blinded for the follow-up allocation.

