#### Effect evaluation primary outcome parameter

To evaluate the difference in clinical effectiveness of both follow-up protocols, the number of radiographs with treatment consequences will be divided by the total number of radiographs in each subgroup (pre-treatment, post-brace, post-surgery). To compare the primary outcome between the PE-FU group and the S-FU group, Pearson’s chi-square test is used. To evaluate the effect according to subgroups, linear mixed-effects models that account for repeated measurements will be performed, adjusted for scoliosis center and relevant baseline covariates. Assumptions of linear mixed modelling will be assessed and if needed variable transformations will be performed. Furthermore, for each subgroup the results of the RCT follow-up protocols will be compared with the similar preference cohort to indicate generalizability of study results.

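### The protocol gives two incompatible allocation rules, minimisation and permuted blocks of 2 and 4; if the blocks are in use, they may be predictable in this open-label trial

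*Protocol article*

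**What the plan says.** All of this is in the protocol article; no separate analysis plan is at hand.

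- **Method, first statement** (Randomization and blinding): "Randomization is performed according to a minimization algorithm in a 1:1 ratio".
- **Method, second statement** (next sentence of the same section): allocation is done in "an online secured study and data-management system" with "built-in randomization (random permuted block size 2:4".
- **Blinding** (same section): "blinding to the follow-up allocation for patients and medical staff is not possible". Only the trial statistician is blinded.
- **Recruiter** (Recruitment and informed consent): "Eligible patients are informed and invited to participate by their local treating orthopedic surgeon".
- **Two routes into the study** (Randomization and blinding): "After obtaining informed consent, patients will either be randomized or allocated to the protocol of their preference". Study design and setting describes the preference cohorts as the place where "all patients are monitored who are not willing to be randomized to either follow-up arm".
- **Centre**: it appears in the analysis of the primary outcome, where the mixed models are "adjusted for scoliosis center and relevant baseline covariates". It is not named as a stratum or as a minimisation factor.

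**The concern.** Minimisation assigns each patient from the current imbalance on chosen factors. Permuted blocks follow a list generated beforehand, in which the arms balance at the end of each block. A reader cannot tell which rule produced the allocations, or which factors the analysis should therefore respect.

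The second issue depends on the answer. Patients and staff see every allocation, and the person who invites the patient is one of those staff. If the list uses blocks of 2 and 4 and the recruiter can follow it, the next arm can often be inferred. A patient who does not enter the RCT can still join a preference cohort, so a diverted patient would remain in the study and the diversion would be hard to see.

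There is a conceivable motive. The patient-empowered arm omits routine intermediate radiographs, and the Discussion (Strengths) accepts that detection of progression might be delayed in the pre-treatment and post-brace subgroups. A surgeon worried about a particular patient might prefer to avoid an expected allocation to that arm. Progression risk drives the primary outcome, so selective entry of this kind would bias the main comparison. Intention-to-treat analysis would not remove that bias, because it arises before randomisation.

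**Working it through.** **The contradiction.** This needs no arithmetic. Two consecutive sentences name two methods, and nothing says how they combine or which governs.

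**Predictability if blocks are used.** The protocol gives no predictability figure to reproduce, and its sample size does not depend on this point. Inputs:

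- Block sizes 2 and 4. This is the natural reading of a terse notation.
- Both sizes equally frequent (assumption).
- 132 patients for a pre-treatment list: 66 per arm × 2 (Sample size).
- 4, 8 or 12 centres of equal size (assumption; the article does not give the number).

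*Step 1. Recruiter sees the whole list.* The guess is the arm that is currently behind, or a coin toss when the arms are level. This needs only a running count, because the count returns to zero at every block end.

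- Block of 2: the first guess scores 1/2 and the second is always right. Expected correct = 1.5 of 2 = 75.0%.
- Block of 4: the first guess scores 1/2. The second is right with probability 2/3. With probability 1/3 the first two are alike and the last two are both right (2). With probability 2/3 the first two differ and the last two score 1/2 + 1 = 1.5. Total = 0.5 + 0.667 + (1/3)(2) + (2/3)(1.5) = 2.833 of 4 = 70.8%.
- Equal mix of 2 and 4: (1.5 + 2.833)/6 = **72.2%**.

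*Step 2. Share of allocations that are certain.*

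- Block ends known: a block of 2 has 1 certain allocation. A block of 4 has on average (1/3)(2) + (2/3)(1) = 4/3. Equal mix: (1 + 4/3)/6 = 38.9%.
- Sizes known but their order hidden, as random mixing implies: a simulation with an optimal guesser gives 8.1%, 9.5%, 10.5% and 11.1% certain for lists of 6, 10, 20 and 132 patients. Correct guesses are 71.0%, 71.5%, 71.8% and 72.2%.

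*Step 3. One list per subgroup shared across centres.* The recruiter sees only patients from the own centre. Simulated with 132 patients, correct guesses are 51.8% (4 centres), 51.1% (8) and 50.8% (12).

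*Step 4. Larger blocks.* Full enumeration gives 68.3% correct for blocks of 6 (25% certain with known ends) and 66.6% for blocks of 8 (20% certain). For an equal mix of 4, 6 and 8:

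- Correct: (2.833 + 6 × 0.6833 + 8 × 0.6661)/18 = 12.262/18 = 68.1%.
- Certain with known ends: (1.333 + 1.5 + 1.6)/18 = 24.6%.

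| Situation (blocks in use) | Correct guesses | Certain allocations |
|---|---|---|
| 2/4 mix, whole list seen, block ends known | at least 72% | 39% |
| 2/4 mix, whole list seen, order hidden | about 72% | 8–11% |
| 2/4 mix, one list shared across centres | about 51–52% | not computed |
| 4/6/8 mix, whole list seen | about 68% | 25% if ends known |

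The 72% and 68% figures are for guessing by running count alone. If minimisation with a random element is the method in use, none of these block figures applies and no allocation is fully certain.

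**The case against.** The inconsistency may be only one of wording. Minimisation might be used loosely for blocks stratified by some factors, and one clarifying sentence would settle it. That may prove true, but the article does not say so, and how patients are allocated is a core design rule. An article that states two conflicting rules is not merely leaving detail to a fuller document.

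The objections to going further are stronger, and most of them stand:

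- A reader might infer that the next allocation is guessable. The document does not support this. It requires that blocks, not minimisation, are in use and that the recruiter can see most of the list. Allocation runs in a central online system, and nothing says that lists are kept per centre.
- A reader might take 39% as the share of certain allocations. That holds only for someone who knows where each block ends, whereas the article describes the blocks as random.
- A reader might conclude that surgeons can steer patients. The preference cohorts are reserved for patients unwilling to be randomised, and no diversion is described. What remains is that willingness is expressed to an unblinded recruiter.
- The absence of minimisation factors, strata or a logging procedure is not a fault in a condensed article.
- The mixed models already adjust for centre, so it would be too strong to say that the analysis cannot adjust for the right factors. The Pearson chi-square comparison of the primary outcome is, however, unadjusted.
- Larger blocks gain little by themselves, and the first patients were included in July 2022, so any change falls part-way through enrolment.

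**Conclusion.** The contradiction is certain: the protocol names two methods that cannot both be the allocation rule. The predictability concern is conditional. If blocks of 2 and 4 are used in equal mix and the recruiter sees the whole list, for example because lists are kept per centre, guesses are right about 72% of the time and about 8–11% of allocations are certain with the order hidden. If each subgroup has one list shared across centres, guesses are right about 51–52% of the time, barely above chance. The document does not say which applies. Selection into the RCTs by expected arm is therefore a possible risk; neither its occurrence nor its effect on the result has been shown. It still deserves correction, because the trial is open label, the treating surgeon recruits, a second route into the study is available after consent, and protection is cheap.

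**What to change.** 1. State the one method actually used, and correct the other sentence.
2. For patients still to be enrolled, if blocks are used: drop the block of 2, use larger randomly varying sizes (for example 4, 6 and 8), and withhold the sizes from the sites.
3. If minimisation is used: include a random element.
4. Under either method, record the choice between RCT and preference cohort irrevocably before the allocation is released.
5. Adjust the primary analysis for the factors used in allocation.

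**Cost.** Item 1 is wording. Items 2 to 4 need a system setting and a step in the enrolment procedure. Larger blocks allow slightly more imbalance within small centres. Changing the scheme part-way through enrolment must be reported and may need notification to the ethics committee as an amendment. The gain from larger blocks alone is modest (about 72% to 68% correct guesses when the whole list is seen), so items 1 and 4 matter most. Sample size is unaffected.

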### Study interventions

#### Patient-empowered follow-up (PE-FU) protocol (Figure 2)

The PE-FU protocol consists of patient-reported outcome measures (PROMs), the Scolioscope and clinical assessment including physical examination by the physician. The Scolioscope is a self-assessment tool that measures the trunk rotation, similar to what is measured with the Bunnell scoliometer (Figure 3). At baseline and at last follow-up (24 months) biplanar radiographs are taken. Instead of routine radiographs, at all intervening follow-up visits radiographs will only be taken when curve progression or postoperative complications are suspected based on so-called “sense of alarm” criteria, which is a signal for the treating physician to consider whether a radiograph is appropriate.

**Figure 2 F0002:**
[figure not shown]
Follow-up scheme for each of the 3 predefined subgroups of the current study with timeline, with time in months from inclusion to radiography, monoplanar (posterior-anterior), or biplanar. S-FU = standard follow-up, PE-FU = patient empowered follow-up.

**Figure 3 F0003:**
[figure not shown]
Angle of trunk rotation measurement using the Scolioscope. © Productzaken

“Sense of alarm” is based on any concern by the orthopedic surgeon, patient, or parent that warrants a radiograph and any deterioration on the PROMs, Scolioscope, and clinical assessments. For both the Bunnell scoliometer and the Scolioscope a threshold of respectively ≥ 4° and ≥ 4 points increase will be used [11]. No known thresholds exist for the included PROMs to support the decision to take a radiograph; the clinical view of the physician is important and included. For all non-protocolized radiographs taken, the reason is reported.

#### Standard follow-up (S-FU) protocol (Figure 2)

The S-FU protocol consists of routine full spine radiographs taken at inclusion and each follow-up visit, to detect possible curve progression or to rule out postoperative complications. For the post-surgical group, biplanar (posterior-anterior [PA] and lateral) radiographs are taken at each follow-up assessment. For pre-treatment and post-brace groups uniplanar radiographs are taken, with biplanar radiographs at baseline and at last follow-up (24 months) visit.

### Patient characteristics and outcome measures (Table 2)

At baseline, relevant patient characteristics are collected to describe the study sample, including the 3 different subgroups. Primary outcome is defined as the proportion of radiographs that has led to treatment consequences in each subgroup (pre-treatment, post-brace, post-surgery). A treatment consequence is defined as start of brace therapy or any surgical intervention. Secondary outcome measures include both patient and clinician-reported outcomes.

**Table 2 T0002:** Baseline characteristics, secondary outcome measures, and measurement moments

Variable	Month of follow-up assessments					
	Baseline	3	6	12	18	24
Post-surgery group	√	√	–	√	–	√
Pre-treatment group and post-brace group	√	–	√	√	√	√
**Baseline patient characteristics**						
Patient-reported and clinician-reported.	√	–	–	–	–	–
Including age, sex, family origin (CBS [24]), BMI, concomitant diseases, concomitant medication, family history of AIS, sports, education status						
**Secondary outcome measures**						
Health-related quality of life (PROM): EuroQol-5						
Dimensions (EQ-5D-5L – Dutch version [25]).	√	√	√	√	√	√
A 5-item questionnaire, consisting of 5 dimensions (mobility, self-care, usual activities, pain/discomfort, and anxiety/depression) QALYs will be estimated using the Dutch tariff [25]						
Condition-specific quality of life (PROM):						
SRS-22r – Dutch version [26]	√	√	√	√	√	√
A 22-item questionnaire, consisting of 5 domains (pain [5 items], self-image [5 items], function ([5 items], mental health [5 items], and satisfaction with management [2 items]) and a total score, with scores ranging 1 to 5 for each item						
Pain (PROM) Numerical Rating Scale (NRS)	√	√	√	√	√	√
Ranging from 0 (no pain) to 10 (worst imaginable pain) for mean pain since last visit						
Spinal appearance questionnaire (PROM): Short SAQ	√	√	√	√	√	√
A 14-item questionnaire [27,28], consisting of a total score and 2 domain scales, “appearance” (10 items) and “expectations” (4 items), with scores ranging from 1 to 5						
Global Perceived Effect (PROM): GPE	√	√	√	√	√	√
2 items ranging in score from 1 to 7 regarding satisfaction with the treatment effect [29]						
Education status (PROM) Patient-reported	√	√	√	√	√	√
Absence from school, absence from physical education (PE) classes, frequency of missing school exams, necessity to repeat a class, support and alternatives provided by the school						
Health-related and societal costs (PROM): Questionnaires	√	√	√	√	√	√
Costs will be collected with cost questionnaires (modified iPCQc , iMCQ, and iViCQ). Resource use will be valued in accordance with the Dutch Manual for Costing Studies in Health Care [30]						
Angle of trunk rotation (ATR, °; patient-reported)						
Scolioscope (only PE-FU)	√	√	√	√	√	√
The asymmetry of the spine results in an ATR and a rib hump, which will be measured by the parent/caregiver						
Curve progression (ATR, °; clinician-reported)						
The Bunnell scoliometer [11]	√	√	√	√	√	√
Patient-reported questions after surgery (post-surgery group only): Return to school, return to sport	√	√	–	√	–	√
Radiographic assessment (full spineradiograph; clinician-reported)	√	√	√	√	√	√
Progression of deformity in the primary and compensatory Cobb angels (°).						
Biplanar radiographs for post-surgery group and at baseline and 24 months for pre-treatment and post-brace groups. According to S-FU monoplanar radiographs are taken during follow-up visits for pre-treatment and post-brace groups						
Radiation exposure:						
Calculation using reference values	√	√	√	√	√	√
Assessment (serious) adverse events (clinician-reported)	–	√	√	√	√	√

**Table 2 T0003:** Abbreviations

PROM = patient reported outcome measure. iMTA = institute for Medical Technology Assessment. iPCQ = iMTA Productivity Cost Questionnaire. iMCQ = iMTA Medical Consumption Questionnaire. iViCQ = iMTA Valuation of Informal Care Questionnaire PE-FU = patient-empowered follow-up protocol. S-FU = standard follow-up protocol.

